#### Drop-out criteria

Patients who refused to cooperate with the test and diagnostic errors after enrollment were considered as excluded cases;During the study period, patients dropped out, did not complete the whole course of treatment, and poor compliance were considered as abscission cases.Patients who could not tolerate acupuncture, had serious adverse events during treatment, or had serious complications caused by other diseases would terminate the trial.

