### Sample size

The calculation of sample size will be based on the change of ISI scores. According to the results of existing published literature (36), the overall standard deviation of ISI scores in patients of hypertension with insomnia was 5.5, ISI scores decreased by 3.3 after treatment, α = 0.05, β = 0.10, and *N* ≈ 24 cases were calculated. Considering the factors of contamination, non-compliance and shedding during the test, the shedding rate was determined to be 20%, so there were 30 cases in the treatment group and 30 cases in the control group. For comprehensive consideration, a total of 60 samples will be required for this study.

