### Informed consent

Participants will be informed of the details of the study, including the purpose of the study, potential benefits and risks, other available treatment options, and participant rights and obligations. Participants will be included in the study after signing written informed consent. If participants drop out of the trial, relevant data will be retained for final analysis.

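### The 20% sample-size allowance treats contamination and non-compliance as lost patients; if such patients are measured and analysed, they dilute the effect and the allowance does not hold 90% power

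*Protocol article*

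**What the plan says.** The Sample size section of the protocol article sizes the trial on a secondary outcome: "The calculation of sample size will be based on the change of ISI scores". Its inputs are that "the overall standard deviation of ISI scores in patients of hypertension with insomnia was 5.5", that "ISI scores decreased by 3.3 after treatment", and "α = 0.05, β = 0.10". From these, "24 cases were calculated". The allowance follows: "Considering the factors of contamination, non-compliance and shedding during the test, the shedding rate was determined to be 20" per cent, which leads to 30 patients in each arm and 60 in all.

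Two other sections bear on what happens to the patients covered by that allowance. Under Drop-out criteria, "patients dropped out, did not complete the whole course of treatment, and poor compliance were considered as abscission cases", a category kept apart from the excluded cases (refusal to cooperate, diagnostic error). Under Informed consent, "If participants drop out of the trial, relevant data will be retained for final analysis". Statistical analysis plans a t-test or rank sum test between the two groups and names no analysis population.

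**The concern.** Three different things are put into one rate and then handled as one thing. A patient with no week-4 score reduces the number analysed, and dividing by (1 − loss) puts that right. A patient who skipped treatment but was measured, or a control who received active treatment elsewhere, stays in the group mean and pulls the contrast towards zero. Offsetting a diluted fraction f requires division by (1 − f)², because the effect enters the sample-size formula squared.

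Read together, Drop-out criteria and Informed consent most naturally keep at least the poor compliers in the final analysis. On that reading, the allowance does not do what it is said to do for two of its three named factors. The power claim then belongs to 24 fully treated patients per arm and not to the set that is analysed. A null result could be read as evidence against acupuncture when part of it reflects dilution.

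**Working it through.** **Inputs.** From Sample size: SD 5.5, effect 3.3 points, α = 0.05, power 90%, allowance 20%, 30 per arm. Assumed, because the article does not give them: how the 20% splits between loss and dilution, and that diluted patients contribute no effect.

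**Reproducing the article's figures.** Of the standard formulas tried, only the one-sample (before–after), one-sided one returns 24:

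- One-sample, one-sided: (1.645 + 1.282)² × 5.5²/3.3² = 23.8, rounded up to 24.
- One-sample, two-sided: 29.2, so 30.
- Two-sample, one-sided: 48 per arm.
- Two-sample, two-sided: 59 per arm.

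The allowance is exact as arithmetic: 24/0.8 = 30. So 24 is a per-arm figure, and all three factors were handled as loss.

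**Power on the article's own basis.** With a loss share l and a diluted share f of the 30 randomised, the number analysed is n = 30(1 − l), the effect is 3.3 × [1 − f/(1 − l)], and power = Φ(effect/5.5 × √n − 1.645).

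| Lost / diluted | n analysed | Effect | Power |
|---|---|---|---|
| 20% / 0% | 24 | 3.30 | 90.2% |
| 15% / 5% | 25.5 | 3.11 | 88.6% |
| 10% / 10% | 27 | 2.93 | 87.0% |
| 5% / 15% | 28.5 | 2.78 | 85.4% |
| 0% / 20% | 30 | 2.64 | 83.7% |

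If nobody is lost and 10% are diluted, the effect is 2.97 and power is 90.5%, so 30 is still enough in that case.

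If all 20% are diluted, the requirement is 23.8/0.64 = 37.2, which rounds up to 38. At 37, power is Φ(0.48 × √37 − 1.645) = 89.9%; at 38 it is 90.6%.

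**Power for the planned two-group comparison** (two-sided t-test, noncentral t, same SD and effect; the article does not state sidedness):

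- 30 per arm, no loss or dilution: 63%.
- 24 per arm, undiluted (all 20% lost): 53%.
- 27 per arm, effect 2.93 (half lost, half diluted): 48.5%.
- 30 per arm, effect 2.64 (all 20% diluted): 45%.

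The fall from 90% to 53% occurs with the allowance working exactly as the article intends, so it comes from the base figure of 24. Counting the 20% as diluted instead of lost takes off about 8 more points (53% to 45%).

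**The case against.** The strongest objection is that retention is inferred. No analysis population is named, the data that count as relevant under Informed consent are not defined, and nothing says how contaminated patients are analysed. If poor compliers left the efficacy comparison, 24/0.8 would be the right correction. The analysis set may also be fixed in a fuller document that is not shown. This stands, and it makes the point conditional. It does not remove it: the article places poor compliers with drop-outs, not with excluded cases, and says that drop-outs' data are kept.

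Second, the 3.3 points come from a published study. If that estimate already reflects ordinary non-compliance, discounting it again would count dilution twice. This stands and belongs in the fix.

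Third, zero effect is a worst case. Someone who misses a few of the 12 sessions may still benefit, and a sham patient who misses sham sessions need not dilute anything. The lower ends of the ranges above are therefore bounds, not forecasts.

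Fourth, a one-sample formula has no control arm, so contaminated controls cannot dilute it. The 83.7% can represent non-compliance only; contamination can be expressed only on the two-group basis. This also stands.

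Finally, a reader might infer that the allowance by itself is why 30 per arm misses 90%, or that 38 per arm would restore it. The documents do not support either. If all 20% are lost, the allowance is correct on its own basis, and the two-group comparison falls far short before any dilution.

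**Conclusion.** The point holds in a conditional form. Dividing by 0.8 protects power only against missing outcomes. To the extent that non-compliant or contaminated patients are measured and analysed, which is the more natural reading for the non-compliant, 30 per arm does not carry the protection claimed for it.

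On the article's own basis the cost runs from nothing to about 6.5 points (90.2% to 83.7%), depending on an unstated split and on the assumption of no effect in those patients. A 15/5 split costs under 2 points. On the planned two-group comparison the difference between pure loss and pure dilution is about 8 points, on top of a larger shortfall that belongs to the base calculation.

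A flat statement that these patients stay in the analysis, or that the allowance always fails to preserve 90%, would go further than the text. The matter is worth correcting because the power figure guides how a null result is read, and because power recomputed at 30 per arm with the full 3.3 points (63%) would still be too high if some analysed patients are diluted.

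**What to change.** Keep 60 patients and revise the Sample size paragraph:

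1. Recompute power for the two-group comparison at 30 per arm, and state whether the test is one- or two-sided.
2. Split the 20% into patients expected to have no week-4 outcome, who reduce n, and patients expected to be measured but non-compliant or contaminated, who reduce the 3.3-point effect. Leave the effect unreduced for non-compliance if the source estimate already reflects it, and say so.
3. Restate the power for the set of patients whose data Informed consent says are kept, and make clear whether the cases classed with drop-outs under Drop-out criteria are in it.

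A shorter alternative is to remove contamination and non-compliance from the list of reasons, state that the 20% covers missing outcomes only, and state that the power assumes full compliance. The base figure still needs recomputing for the two-group comparison.

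The cost is one reworded paragraph and a less favourable stated power. No extra patients or procedures are needed.

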### Randomization and allocation concealment

After screening by inclusion and exclusion criteria, eligible participants will be divided into the treatment group and the control group according to the ratio of 1:1 by block random method, with 30 cases in each group. Random sequences will be generated using SPSS 25.0 software (IBM, Armonk, NY, USA) by researchers who are not involved in the implementation and statistical analysis of the experiment.

### Blinding

Grouping results will be kept confidential to participants, evaluators and statisticians. All participants will be asked to indicate whether they have received acupuncture or sham acupuncture within 5 min of treatment to assess blindness. Because the acupuncturist is required to perform acupuncture interventions, the grouping results will not be kept secret from the acupuncturist, the acupuncturist will not be able to evaluate the intervention results, and the evaluator will not be allowed to discuss the treatment.

### Informed consent

Participants will be informed of the details of the study, including the purpose of the study, potential benefits and risks, other available treatment options, and participant rights and obligations. Participants will be included in the study after signing written informed consent. If participants drop out of the trial, relevant data will be retained for final analysis.

### Safety monitoring

Adverse events (AEs) during treatment will recorded in a timely manner, including local hematoma, dizziness, and stagnation of acupuncture. Any serious AEs associated with the trial will be immediately reported to the main researchers, and we will determine its cause, analyze its correlation with acupuncture, and treat symptomatically.

### Data collection and management

Data from subjects was collected using the case report form (CRF) designed for this study and backed up into a database based on observed indicators. The Archives of Jiangsu Provincial Hospital of Traditional Chinese Medicine will keep these data for more than 10 years, during which time only members of the research team have access to these data.

### Statistical analysis

In this study, all statistical analyses will be conducted by an independent statistician using SPSS 25.0 software (IBM, Armonk, NY, USA). The measured data will be expressed as mean ± standard deviation, and the count data will be expressed by the ratio or composition ratio. For comparing measured data between the two groups, first normal analysis will be performed. A *t*-test will be used for the measured data conforming to normal and homogeneity of variance, and a nonparametric rank sum test will be used for non-normally distributed measured data. The data will be counted by the Chi-Square test or Fisher's exact test. *P* values ≤ 0.05 will be considered statistically significant.

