### Outcome measures

#### Primary outcome measures

PPSG is one of the sleep monitoring methods with the advantages of supporting home environment monitoring and avoiding the influence of the first night effect, which can be used for objective diagnosis of insomnia, treatment evaluation and differential diagnosis of sleep diseases. In this study, Anbaolan wearable portable sleep recorder [202070644; Embla (Beijing) Medical Equipment Co., Ltd., Beijing, China] was applied to sleep monitoring. The device records electroencephalogram (EEG), electrooculogram (EOG) and electromyogram (EMG) signals through a set of head-mounted sensors, monitors blood oxygen with finger pulse oxygen, and uses AI intelligent algorithms to evaluate sleep structure in detail, including wakefulness (W) and rapid eye movement sleep (REM) sleep period), N1 stage sleep, N2 stage sleep, N3 stage sleep, and then the sleep quality evaluation indicators such as sleep efficiency (SE), sleep awakening times (SA) and total sleep time (TST) can be obtained, which can provide real-time and objective sleep evaluation indices for individuals. Sleep parameters of PPSG will be collected one night and evaluated before treatment and after 4 weeks of treatment.

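### The only between-group tests named take no baseline covariate although every continuous efficacy outcome has a baseline; ANCOVA would be more precise, by an amount the documents do not fix

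*Protocol article*

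**What the plan says.** All references are to the protocol article. Under Statistical analysis, the choice of test starts from a distribution check: "For comparing measured data between the two groups, first normal analysis will be performed". Data that pass for normality and equal variance go to a t-test; for the rest, "a nonparametric rank sum test will be used for non-normally distributed measured data". The section names no covariate or regression model. It also does not say whether the quantity compared is the week-4 value or the change from baseline. The Discussion adds age stratification and subgroup analysis, which is not adjustment for the baseline of the outcome.

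Every continuous efficacy outcome has a pre-treatment value. For the primary outcome: "Sleep parameters of PPSG will be collected one night and evaluated before treatment and after 4 weeks of treatment". Under Secondary outcome measures, PSQI, ISI and HRV are each taken before and at the end of treatment, and the sleep and blood-pressure diary starts one week before treatment.

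The Sample size section gives the only figures from which power can be worked out: "The calculation of sample size will be based on the change of ISI scores", with "the overall standard deviation of ISI scores in patients of hypertension with insomnia was 5.5", "ISI scores decreased by 3.3 after treatment" and "α = 0.05, β = 0.10". This leads to 24 cases, raised to 30 per group because "the shedding rate was determined to be 20" per cent.

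**The concern.** The trial is small: 30 per arm, 24 if the expected losses occur. At that size a chance difference between arms at baseline can be appreciable, and a test on week-4 values carries it into the estimate in proportion to the correlation between baseline and week 4. A test on change removes the baseline but over-corrects when that correlation is modest. ANCOVA estimates the right amount of correction from the data.

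Two further features follow from the text. Choosing the test by a normality check makes the method depend on the data. The rank-sum branch on its own gives a P value but no difference on the scale of the outcome, such as minutes of sleep, ISI points or mmHg.

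What is at stake is precision and a clear effect estimate. The validity of the comparison is not in question.

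**Working it through.** **Inputs from the documents (Sample size).** Difference 3.3 and SD 5.5 ISI points, so d = 3.3/5.5 = 0.60. Alpha 0.05 (sidedness not stated; two-sided used here), power 90%, 24 evaluable per arm.

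**Assumed.** The correlation r between baseline and week 4 is given for no outcome, so a range of 0.4 to 0.7 is shown. SDs are taken as equal at both times and in both arms. The 3.3 is worded as a fall after treatment; it is used here as a difference between arms.

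**The plan's own figure.**
- Two-group, two-sided: n = 2 × ((1.960 + 1.282)/0.60)² = 58.4, so 59 per group.
- Two-group, one-sided: 2 × ((1.645 + 1.282)/0.60)² = 47.6, so 48 per group.
- One-sample, one-sided: ((1.645 + 1.282)/0.60)² = 23.8, so 24.

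The stated 24 appears only from the last formula, which does not compare two groups. The step for losses does reproduce: 24/0.8 = 30. This sizing problem is separate from the present point, but it sets the starting level of power.

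**Power of the t-test.** The noncentrality is d/√(2/n) = 0.60/√(2/24) = 2.08, with 46 degrees of freedom. This gives 53.0% (about 63% if all 30 per arm are evaluable).

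**Reading A: 5.5 is the SD of the score.** The standardised difference becomes 0.60/√(2(1 − r)) for change scores and 0.60/√(1 − r²) for ANCOVA.

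| r (assumed) | t-test, week 4 | t-test, change | ANCOVA |
|---|---|---|---|
| 0.4 | 53% | 46% | 60% |
| 0.5 | 53% | 53% | 65% |
| 0.6 | 53% | 62% | 72% |
| 0.7 | 53% | 75% | 81% |

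**Reading B: 5.5 is the SD of change.** The change-score test then has d = 0.60 and 53% power whatever r is. The ANCOVA residual SD is 5.5 × √((1 + r)/2), so its standardised difference is 0.60/√((1 + r)/2).

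| r (assumed) | t-test, change | ANCOVA |
|---|---|---|
| 0.4 | 53% | 68% |
| 0.5 | 53% | 65% |
| 0.6 | 53% | 62% |
| 0.7 | 53% | 60% |

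The two readings run in opposite directions: under A the gain over the week-4 test rises with r, and under B the gain over the change test falls with r.

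**Small-sample cost of the covariate.** ANCOVA has 45 instead of 46 degrees of freedom, which alone costs less than 0.1 point. Estimating the slope inflates the variance by about 1 + 1/(48 − 4) = 1.023. Together they take about 1 point off each ANCOVA figure above. At r = 0 ANCOVA has about 52.0%, and at r = 0.1 about 52.5%, against 53.0% for the week-4 t-test.

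**Share of the shortfall closed (Reading A, against the week-4 test).** The gap to the stated 90% is 90 − 53 = 37 points. ANCOVA closes (60 − 53)/37, about a fifth, at r = 0.4; (65 − 53)/37, about a third, at r = 0.5; and (81 − 53)/37, about three quarters, at r = 0.7. By the normal approximation, reaching 90% with 24 per arm needs r of about √(1 − 24/58.4) = 0.77.

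**The case against.** The strongest objection is that nothing here is wrong. In a randomised trial a t-test or rank-sum test is valid without adjustment, and a condensed article may leave the analysed quantity, the treatment of unequal variances and the form of the effect estimate to a full plan. That stands as far as validity goes, and those details are not relied on here. It does not remove the point, because the article names the tests. A later plan that used ANCOVA would depart from the published method.

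Four stronger readings are tempting, and the documents do not support them.

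- A reader might infer that the planned tests ignore the baseline altogether. The text does not say so. The sample size is based on change in ISI, and a t-test on change does use the baseline. ANCOVA still does better at every r tabulated, but by less than against a week-4 test where r is above 0.5.
- A reader might infer that ANCOVA would recover most of the missing power. That depends on r, which is not given, and on whether 5.5 is the SD of the score or of change. At r = 0.7 the two readings give 81% and 60%.
- A reader might carry these figures over to the primary outcome. They are for ISI, a secondary outcome. No effect, SD or correlation is given for any PPSG parameter, and a single night at each visit may correlate weakly. Under Reading A, r = 0.3 gives only about 4 points over the week-4 test.
- A reader might call ANCOVA never worse and free of cost. With r near zero it loses about 1 point.

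**Conclusion.** The point holds as one of efficiency and reporting. The article names only tests without a covariate, selected by a normality check, although a baseline value exists for every continuous efficacy outcome. For ISI at 24 per arm, ANCOVA raises power from 53% for a week-4 test to about 60–81% over r = 0.4 to 0.7 if 5.5 is the SD of the score. If 5.5 is the SD of change, it raises power from 53% for a change test to about 68–60% over the same range. About 1 point comes off each ANCOVA figure for the small sample. Over this range ANCOVA gains whether week-4 values or changes would have been tested, but the amount rests on an assumed correlation and an ambiguous SD. For the PPSG parameters the gain cannot be quantified. Power for the rank-sum branch was not calculated. Adjustment does not make 24 per arm an adequate size for the stated 90% power; that calculation needs its own correction.

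**What to change.** Before unblinding, amend the Statistical analysis section, or fix it in the analysis plan and record the change, as follows:

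- The main analysis of each continuous outcome is an ANCOVA of the week-4 value on treatment, with the baseline value of that outcome as covariate, reported as the adjusted difference with its 95% CI.
- For skewed outcomes, use a transformation or robust or bootstrap standard errors, chosen by outcome in advance.
- The normality check no longer selects the test. The t-test and rank-sum test stay as sensitivity analyses, with the quantity they compare (week-4 value or change) stated.
- For home blood pressure, name the diary summaries that serve as the baseline and final values.

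The cost is a change of wording. No extra patient, visit or measurement is needed, and SPSS 25.0, already the planned software, fits the model. The statistical price is one degree of freedom and a loss of about 1 point of power if baseline and week 4 turn out nearly uncorrelated.

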### Quality control

To guarantee the quality of the trials, all participants, including acupuncturists, evaluators, and statisticians, will receive unified training. Acupuncturists with a master's degree in medicine, licensed physicians and clinical experience must strictly implement standardized intervention procedures. To familiarize the treatment options, all physician assistants are required to undergo a one-day professional training. To ensure consistency across the different participants, we will develop a set of clinical management practices. The above can ensure the feasibility and safety of clinical research.

### Trial status

The current protocol version is 2.0 as of 9 December 2021. The randomization began (recruitment) on 1 June 2022. Recruitment is expected to end in late 2022.

## Discussion

This study, a single-center, subject-and-assessor-blind, randomized, sham-controlled trial, aims to evaluate the efficacy of acupuncture using the PPSG combined with sleep scales, and to analyze HRV-related data to preliminarily explore the underlying mechanism of acupuncture in patients of hypertension with insomnia.

Insomnia is closely related to hypertension, which often exists in the form of comorbidity, seriously affecting patients' quality of life, physical and mental health, and increasing social medical burden. Acupuncture is widely used owing to its unique merits of simplicity, safety, and few side effects, which has potential advantages in the treatment of hypertension and insomnia (20, 37–39). However, there are few high-quality clinical studies on the intervention of acupuncture on hypertension with insomnia, and the following problems are common. First of all, the evaluation indicators of sleep are mainly based on subjective scales. Therefore, PPSG is first applied to the trail to assess objective sleep parameters. Secondly, the types of hypertension medication have been not clearly specified and limited in most studies. But researches have shown that beta-blockers such as metoprolol may reduce nocturnal melatonin production by blocking 5-HT, thus leading to increased number of awakenings, prolonged sleep latency and decreased sleep efficiency (40, 41). And diuretics give rise to increased number of nocturia and increased number of awakenings, which further leads to insomnia. Hence, this study will restrict the types of hypertension drugs, and the included patients will be only permitted to taken CCB+ACEI/ARB, so as to minimize the impact of hypertension drugs on sleep.

Thirdly, excessive activation of the sympathetic nervous system may be one of the mechanisms of the comorbidity of insomnia and hypertension (26, 27). HRV is a biological indicator reflecting the functional status of human sympathetic and parasympathetic nerves (41). Previous studies have shown that the nighttime HRV of insomnia patients is lower than that of healthy people (42), accompanied by increased heart rate, elevated blood pressure and other manifestations of enhanced sympathetic response (26, 43, 44). Meanwhile, elevated sympathetic activity is pivotal in the pathogenesis of hypertension (45). HRV parameters showed a strong correlation with hypertension, especially the time-domain index of HRV showed a significant negative correlation with hypertension (46). Lan et al. (47) used six HRV parameters to predict hypertension, and found that SDNN (one of the time-domain indicators) had the best predictive ability. Therefore, HRV, especially time-domain indicators, may be a potential marker reflecting the increased risk of hypertension in patients with insomnia. However, there is no research to explore the mechanism of acupuncture in the treatment of hypertension with insomnia, so this study used the change of HRV to initially explore the potential mechanism of acupuncture on the comorbidity of hypertension and insomnia.

Finally, in order to eliminate the placebo effect of acupuncture treatment as much as possible, sham acupuncture was used as a control in this study to reduce bias. According to the theory of traditional Chinese medicine, the main mechanisms of insomnia are Yin and Yang disorder, spirit falling to be nourished, and absence of mind. Hence, we choose DU20 (Baihui) and EX-HN3 (Yintang) which are located in the head and belong to the Du meridian to regulate the brain and calm the spirit, choose HT7 (Shenmen) points belonging to the heart meridian to calm the mind and take the intersection point of the three Yin meridians of foot to reconcile Yin and Yang. Considering that the primary pathogenesis of hypertension is deficiency of kidney Yin and hyperactivity of liver Yang, LR3 (Taichong) point of liver meridian is added to tranquilizing liver Yang and KI3 (Taixi) point of kidney meridian to nourish kidney Yin. According to the theory of TCM and some previous studies, acupuncture at the above points can solve the related symptoms of insomnia (48) and reduce blood pressure (49).

However, there are still some limitations in this study. (1) There is no follow-up in this study due to the limited conditions. However, it is necessary to observe the long-term effects of acupuncture on regulating blood pressure and improving sleep quality because most patients have a long course of disease and are difficult to cure, whether it is hypertension or insomnia. (2) The single-center experimental design will result in a single sample, with limited representativeness, and possible experimental bias. More influencing factors should be considered and the result should be further verified and explored in a large sample population. (3) The patients included in this study ranged from 18 to 70 years old, which might affect the results owing to the hypertension and insomnia rates of the elderly were higher than those of the young. Therefore, age stratification and subgroup analysis will be conducted during the result analysis. (4) The blood pressure data collection in this study is home self-measured blood pressure. Due to the limitation of the subject equipment, the 24-h ambulatory blood pressure changes of the patients, especially the nighttime blood pressure changes, could not be collected. But studies have shown that blood pressure indicators associated with increased risk of cardiovascular disease are nighttime, 24 h, daytime, home self-assessment, and office blood pressure in order of correlation (50). And there is currently evidence to support (51) insomnia as a risk factor for nocturnal hypertension and abnormal blood pressure rhythms. Therefore, it is necessary to pay attention to the blood pressure during sleep in patients with hypertension and insomnia. In the future, smart wearable devices that can regularly monitor patients' 24-h blood pressure and sleep can be used to further investigate the effect of acupuncture on hypertension with insomnia.

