## Methods/design

### Design

A single-center, subject-and-assessor-blind, randomized, sham-controlled trial will be performed at Jiangsu Province Hospital of Chinese Medicine (Nanjing, China). A total of 60 participants will be randomly assigned to the treatment group (acupuncture group) and the control group (sham acupuncture group) in a 1:1 allocation ratio. Both groups will be treated three times per week for 4 weeks (12 sessions totally). The clinical trial conforms to Standard Protocol Items: Recommendations for Interventional Trials (SPIRIT) 2013 statement (33) as well as the Standards for Reporting Interventions in Controlled Trials of Acupuncture (STRICTA) (34). The study procedure and details are summarized in Figure 1 and Table 1.

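### Age subgroup analysis in 60 patients does not suit the prognostic concern it is meant to answer, and separate tests by age group could easily mislead; an age-adjusted overall comparison would serve better

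*Protocol article*

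**What the plan says.** The Discussion lists the age range of 18 to 70 as its third limitation. The reason is that age is something "which might affect the results owing to the hypertension and insomnia rates of the elderly were higher than those of the young". The response follows at once: "Therefore, age stratification and subgroup analysis will be conducted during the result analysis".

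Three other parts of the Protocol article bear on this:

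- **Design and Randomization:** "A total of 60 participants will be randomly assigned to the treatment group (acupuncture group) and the control group (sham acupuncture group) in a 1:1" ratio. Patients are allocated "according to the ratio of 1:1 by block random method, with 30 cases in each group". No age strata are mentioned.
- **Sample size:** the trial is sized on the ISI, with no allowance for age groups. The inputs are that "the overall standard deviation of ISI scores in patients of hypertension with insomnia was 5.5" and that "ISI scores decreased by 3.3 after treatment", with "α = 0.05, β = 0.10, and *N* ≈ 24 cases were calculated".
- **Statistical analysis:** the between-group methods described are the t-test, the rank sum test, and the chi-square or Fisher test. The general rule is that P "values ≤ 0.05 will be considered statistically significant". Age does not appear in that section.

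**The concern.** The remedy does not follow from the reason. The inclusion criteria require both insomnia and primary hypertension, so the higher frequency of these conditions among older people in the population gives no ground to expect a different treatment effect by age. At most, older and younger participants may differ in their outcomes whichever treatment they receive. That calls for accounting for age in the overall comparison. Subgroup analysis answers a different question: whether the effect itself varies with age.

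The practical risk lies in how the subgroups would be judged. The only tools the article describes are unadjusted two-group tests with a significance threshold. If each age group is tested that way, one group may cross the threshold and the other not, purely because both tests are weak. Such a result is easily reported as acupuncture working only in the younger or only in the older patients, although the two effects are the same.

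**Working it through.** **Inputs from the article (Sample size, Design).** ISI difference 3.3 and SD 5.5, so d = 3.3/5.5 = 0.6. There are 30 patients per arm, or 24 per arm after the stated 20% loss.

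**Assumptions not in the article.** Two age strata of equal size, balanced between arms; two-sided tests at 0.05; 3.3 read as a between-group difference, although the article words it as a fall after treatment.

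**The plan's own figure.** The stated 24 is reproduced by a one-sample, one-sided formula: (5.5 × (1.645 + 1.282)/3.3)² = 23.8, rounded up to 24. Then 24/0.80 = 30 per arm, 60 in all. Of the variants tried, no other gives 24: one-sample two-sided gives 29.2, two-sample one-sided 48 per arm, and two-sample two-sided 59 per arm. Read as a two-sided comparison of two groups, the whole trial has about 63% power with 30 per arm and 53% with 24 per arm (noncentral t). The subgroup figures start from that level.

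**Power within one age stratum.** With n per arm per stratum, the two-sample t-test has noncentrality d × √(n/2) on 2n − 2 degrees of freedom.

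- 48 analysed, n = 12: 0.6 × √6 = 1.470, 22 df, power 29.0%.
- 60 analysed, n = 15: 0.6 × √7.5 = 1.643, 28 df, power 35.5%.

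**Same true effect in both strata.** The strata are independent. With power p in each, the chance that exactly one is significant is 2p(1 − p), and that both are is p².

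| Analysed | p | Exactly one | Both | Neither |
|---|---|---|---|---|
| 48 | 29.0% | 2 × 0.290 × 0.710 = 41.2% | 8.4% | 50.4% |
| 60 | 35.5% | 2 × 0.355 × 0.645 = 45.8% | 12.6% | 41.6% |

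The misleading pattern is thus about four to five times as frequent as significance in both groups (41.2/8.4 and 45.8/12.6). Unequal strata change little. A one-third/two-thirds split gives 42.6% (48 analysed) and 47.8% (60 analysed); a 20/80 split of 60 gives 52.1%.

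**No effect in either stratum.** At least one significant: 1 − 0.95² = 9.75%.

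**Interaction test.** The difference between the two stratum effects has standard error √(4/n) SD, that is 0.577 SD (n = 12) or 0.516 SD (n = 15). If the strata differ by 0.6 SD, as much as the whole design effect, the noncentrality is 1.04 on 44 df or 1.16 on 56 df. Power is 17.4% or 20.8%.

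All figures are for one outcome. The article lists several sleep parameters, two sleep scales, home blood pressure and four HRV indices, so repeating age tests across them gives more openings for a chance pattern.

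**The case against.** The strongest reply is that a single sentence in a limitations list is being read as a detailed testing plan. It gives no cut-point, number of strata, test or significance rule for the age groups. Cut-points and an interaction test may well stand in the full protocol or analysis plan, which are not shown. This stands: their absence is not counted here, and the figures above are conditional on separate testing.

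A reader might go further in four ways that the article does not support.

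- **That the plan leaves age unaccounted for.** The sentence names age stratification as well as subgroup analysis. An analysis stratified by age and pooled over strata would account for age; only separate subgroup tests would not. The article does not say which is meant.
- **That a spurious one-group result is likely.** At 41% to 46% it is below even odds with equal strata, and it needs a real common effect. With no effect the comparable risk is about 10%.
- **That the analysis is post hoc.** It is announced in advance, and nothing presents it as confirmatory or as replacing the overall comparison.
- **That randomisation should have been stratified by age.** Unstratified allocation is no error; any age imbalance arises by chance.

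Two further points also stand. The 0.6 SD belongs to the ISI, a secondary outcome, and the article gives no effect size or SD for the primary sleep parameters. And much of the low power in the strata is inherited from the overall sample size, which gives only about 53% to 63% on the same inputs.

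None of this makes subgroup analysis a suitable answer to a prevalence argument. That mismatch is in the published text and does not depend on what another document may add.

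**Conclusion.** The point holds in limited form. The article commits to an age subgroup analysis on grounds that support age adjustment and not effect modification, in a sample where significance within an age group says little. If the groups are tested separately at P ≤ 0.05, each test has about 29% to 35% power, and an identical effect at all ages would appear significant in exactly one group in about 41% to 46% of trials per outcome. This rests on two equal strata, two-sided testing and the ISI design effect carried over as a between-group difference. Severity is minor, because the analysis is secondary and appears only among the limitations.

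**What to change.** Replace the sentence with two commitments. First, the overall between-group comparison will be adjusted for age as a continuous covariate, for example by ANCOVA that also includes the baseline value of the outcome. Second, one treatment-by-age interaction estimate will be reported with its 95% CI, labelled exploratory, with no significance claims within age strata.

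No new data are needed, since eligibility already depends on age. The cost is more than a change of words: a regression model must be added to a plan that now describes only t-tests and rank sum tests, and the plan should say how that model relates to them. The interaction estimate will be imprecise (about 17% to 21% power for a 0.6 SD difference between two equal strata), so a non-significant interaction must not be read as proof that the effect is the same at all ages.
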